### Setting and Sample

Our study settings are community-based continuing care systems. Each province provides access to a range of publicly funded community-based continuing care services, including adult day programs [55-63]. Each provincial health system determines and enacts access criteria and provides services (directly or via contracted providers) [55-63]. Day program eligibility is assessed in each province, using comparable processes, criteria, and assessments (ie, the Resident Assessment Instrument—Home Care [RAI-HC], a standardized, valid, reliable assessment tool [64]) [60,65,66]. To be eligible, attendees need to have not only some care dependency but also the ability to cope to some extent with activities of daily living, ambulate or transfer with no or minimal assistance, be continent or independent in managing continence products, exhibit no or easily manageable responsive behaviors, and either be alone for extended periods or have a caregiver who requires respite. Our study cohort will include all individuals aged 65 years or older with an initial RAI-HC assessment completed between January 1, 2012, and December 31, 2021. We will follow everyone until they move into a care home, are lost to follow-up (eg, because of death, moving out of province, loss of public insurance eligibility), or until December 31, 2024 (the end of the period covered by our data). That will allow for a care trajectory of at least 3 years (for those with an initial RAI-HC assessment in December 2021), enabling us to assess the number and characteristics of individuals with different day program use patterns, and compare them with those who were never exposed to a day program.

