### Study Variables

#### Exposure

Our exposure will be different patterns of day program use or nonuse, based on information from the provincial continuing care registries, documenting the dates a person starts or stops attending a day program, days of attendance, and the duration of each visit. Day program use patterns will be determined, using LCAs (see *Statistical Analyses* section) [71]. We will categorize three continuous variables as low, low-moderate, high-moderate, or high use, using sample distribution quartiles: (1) time between first RAI-HC assessment and first attendance of a day program; (2) average number of hours of day program attendance (ie, total number of hours spent in a day program divided by the number of times attended); and (3) total number of days a person attended a day program. LCAs will also include a categorical variable, indicating whether a person consistently attended a day program or whether there were longer periods (several weeks) of nonattendance. Nonuse will be defined as no day program exposure at any time during a person’s continuing care trajectory.

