#### Study Outcomes

The data sources noted above enable us to examine a range of important study outcomes. Data on the time between a person’s first RAI-HC assessment and admission to a care home will come from provincial continuing care registries. Symptoms of depression will be assessed using the validated RAI-HC Depression Rating Scale [72], with scores ranging from 0 to 14 and a cut point of 3 or higher representing clinically meaningful depressive symptoms [72,73]. We will capture physical and cognitive decline, using validated RAI-HC scales [64]: the Activities of Daily Living Hierarchy (ADLh) Scale [74] and the Cognitive Performance Scale (CPS) [75]. Both scales range from 0 (no impairment) to 6 (maximum impairment), and our outcomes will be dichotomous, indicating any increase (vs no change or a decrease) between the previous and follow-up measurement in each of these scales. Using care practitioner claims data, we will generate rates of different types of primary and specialist care use (eg, family physician, specialists, nursing practitioner, and allied health providers). We will use the DAD and NACRS databases to generate rates of emergency department registrations, hospital admissions, and days in hospital (including alternative level of care) [43]. Rates will be stratified by day program use or nonuse pattern.

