#### Propensity Score–Matching Variables

To compare outcomes between day program attendees and nonattendees, we will use propensity score matching [78] (for details, see Statistical Analyses section). Propensity scores aim to ensure a similar distribution of baseline variables among treatment (day program attendees) and control (nonattendees)—akin to what random assignment aims to accomplish in randomized trials [78]. Since we lack evidence on differences between day program attendees and nonattendees, our objective 2 analyses will be key to informing the selection of the exact covariates that will form the propensity score. We will derive covariates for day program attendees from the RAI-HC day program eligibility assessment (index date). For each day program attendee, we will identify potential matches as nonattendees whose first RAI-HC assessment was completed within ±3 months of the attendee’s index date (ie, admission to long-term home care at about the same time). This RAI-HC assessment will provide the relevant covariates to enable propensity score matching with day program attendees as of their index date.

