#### Objective 3: Assess Effects of Day Programs

To create a propensity score, we will run a logistic regression for each province with day program attendance or nonattendance as the dependent variable and adding matching covariates. We will use one-to-one matching (1 matched nonattendee for every attendee) [78]. We will use matching without replacement [85] and apply an optimal caliper matching algorithm [86]. As per best practice recommendations [87], we will use a caliper width of 0.2 of the SD of the propensity score’s logit. If this matching approach does not allow us to achieve a sufficient sample size, we will use propensity score quintiles for matching.

We will compare sample characteristics and study outcomes between attendees and nonattendees in every year and province, using bivariate statistical tests (eg, chi-square test or Fisher exact test for categorical variables, *t* tests, or ANOVAs for continuous variables, and their nonparametric equivalents if variables violate statistical assumptions). To assess the effect of day program exposure on time to care home admission, we will specify a multilevel time-to-event model with a health region–level random effect [88]. Health systems in each of the 3 provinces are divided into 5 health regions [89-91], and regional policies may cause clustering effects that our models must account for. Each model will include day program use or nonuse class as independent variable and will be adjusted for time-varying variables. These will include matching variables, if appropriate (ie, in case of group differences in matching variables over time or due to missing data) [80-82] and, if needed, additional covariates (eg, demographics, social determinants, medical or functional conditions, and non–day program community care). Covariates that differ between attendees and nonattendees with a *P* value of ≤.15 in the bivariate analyses will be considered for inclusion. We will add covariates stepwise, one-by-one, and remove those that cause collinearity issues or decrease model fit. As in objective 2, we will pool provincial effects statistically, using random-effects mixed regression models.

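### Objective 3: whole-trajectory nonuse, an outcome timed from the first RAI-HC and a fixed use class push the care home hazard ratio below 1 even if day programs do nothing

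*Protocol article*

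**What the plan says.** Four statements in the Protocol article fix the comparison.

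- **Control group** (Exposure): "Nonuse will be defined as no day program exposure at any time during a person’s continuing care trajectory".
- **Outcome timing** (Study Outcomes): "Data on the time between a person’s first RAI-HC assessment and admission to a care home will come from provincial continuing care registries". No other origin is given for this outcome.
- **Delay to exposure** (Exposure): the first input to the latent classes is the "time between first RAI-HC assessment and first attendance of a day program", cut at quartiles. Another input is the "total number of days a person attended a day program".
- **Model term** (Objective 3: Assess Effects of Day Programs): "Each model will include day program use or nonuse class as independent variable and will be adjusted for time-varying variables". The text that follows lists the time-varying variables as matching variables and further covariates. Attendance is not among them.

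Follow-up ends at the outcome or at loss, which includes death (Setting and Sample): "We will follow everyone until they move into a care home, are lost to follow-up".

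An index date does appear under Propensity Score–Matching Variables: "We will derive covariates for day program attendees from the RAI-HC day program eligibility assessment (index date"). Potential controls are nonattendees whose first RAI-HC fell within 3 months either side of that date. The section uses the date to take covariates and to find matches.

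**The concern.** Two biases combine, and both favour the program.

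1. **Immortal time.** The interval from first RAI-HC to first attendance is credited to the attendee group, yet no one in that group can be admitted or die during it. Otherwise they would not be attendees.
2. **Selection of controls on their future.** A person who would have attended, but is admitted or dies first, is classed as a nonuser. Early admissions therefore collect in the control group.

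The latent classes repeat the problem within attendees. A high total of days attended, or a late first attendance, is possible only for someone who remained in the community long enough.

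At stake is the effect on which the sample size is based. Matching on baseline covariates does not remove either bias, and a large sample only narrows the interval around the wrong value. The Limitations section does not mention it.

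**Working it through.** **The plan's own figure.** The article requires 1327 participants for a hazard ratio of 0.6 (alpha 0.05, power 0.8, covariate R-squared 0.25). Schoenfeld's formula, two-sided and 1:1, gives 4 × (1.960 + 0.842)² / (ln 0.6)² = 120.3 events, and 120.3 / 0.75 = 160.4. A total of 1327 then implies an event probability of 160.4 / 1327 = 12.1%. None is printed, so 1327 is attainable but can be neither confirmed nor called wrong. It serves here only to show the target, 0.6.

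**Inputs for the bias.** The article gives no waiting time, admission rate or death rate, so these are assumptions: admission a = 0.12 per year, death 0.15 per year (total exit rate h = 0.27), exponential waits with start rate s = 1/(mean wait), and a share q = 10-35% who would attend if still in the community. That share fits the article's statement that potential matches greatly outnumber attendees. Entry from 2012 to 2021 with data to the end of 2024 gives 3 to 13 years of potential follow-up.

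**Hand check: 12-month mean wait (s = 1), no program effect, administrative censoring ignored.**

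- Attendees: the pre-attendance time of those who do attend averages 1/(s + h), and the time afterwards averages 1/h. Their admission rate relative to the true rate a is (s + h)/(s + 2h) = 1.27/1.54 = 0.825.
- Nonusers: relative rate = [(1 − q)/h + q/(s + h)] / [(1 − q)/h + qh/(s + h)²].
  - q = 0.10: (3.333 + 0.079)/(3.333 + 0.017) = 1.02.
  - q = 0.35: (2.407 + 0.276)/(2.407 + 0.059) = 1.09.
- Rate ratio: 0.825/1.02 = 0.81 and 0.825/1.09 = 0.76, where the true ratio is 1.

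Most of this is immortal time; the rest is selection of controls.

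**Simulated Cox hazard ratio, same inputs with administrative censoring, ever against never attendance, clock at first RAI-HC, true value 1:**

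| Mean wait | Null HR, 10% to 35% would attend |
|---|---|
| 1 month | about 0.97-0.95 |
| 3 months | 0.92-0.89 |
| 6 months | 0.88-0.82 |
| 12 months | 0.77-0.72 |
| 24 months | 0.68-0.62 |

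The Cox values lie somewhat below the hand-calculated rate ratios.

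**Does the method of analysis cause it?** In a separate set (admission 0.05 to 0.20 per year, death 0.12 per year, 40% would attend, median waits 0.25 to 2 years), coding attendance as time-varying returned 0.99-1.01. Moving only the attendees' clock to first attendance, with never-users still at first RAI-HC, left 0.86-0.97, because selection on never attending remains.

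**Does the index date repair it?** If both clocks started at the index date, a mean wait of 3 to 6 months from eligibility to attendance would still give 0.91-0.81 (10-35% would attend). With the article's calendar matching, a mean of 6 months to eligibility and 6 more to attendance gave 0.69-0.77 on the first RAI-HC clock and 0.78-0.87 on the index-date clock.

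**Precision.** The article expects over 20,000 attendees per year. Take one year's number only, matched 1:1, at the implied 12.1% event probability: 40,000 × 0.121 = 4,840 events, and the standard error of the log hazard ratio is about 2/√4,840 = 0.029. A null value of 0.92 (ln = −0.083) is then 0.083/0.029 = 2.9 standard errors from 1. Pooling three provinces with random effects would widen this somewhat; the article's figure of over 200,000 attendees would narrow it.

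**The case against.** The strongest reply concerns the time origin. The Study Outcomes sentence says where the time data come from, and the Objective 3 text names no time zero for the model. An index date exists. It coincides with the first RAI-HC for controls, and the article describes matched pairs as entering long-term home care at about the same time. A fuller plan might start the clock there. This stands as an ambiguity, but it does not clear the design. The article never moves the clock to the index date, and if it did, the wait from eligibility to attendance and the selection on never attending would remain. The article itself cites a shortage of spaces, so some wait is likely.

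The second reply is that the size is unknown. That is right. If eligibility is usually assessed at the first RAI-HC and attendance follows within weeks, the bias is a few percent.

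A reader might infer that bias alone would deliver the planned hazard ratio of 0.6. The documents do not support that. Values near 0.6 need mean waits of about two years. Figures as low as 0.52 need some 60% of the cohort to be would-be attendees, which conflicts with the article's statement that potential matches far outnumber attendees.

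A reader might also infer that the nonuse definition is wrong throughout. It is not: objective 2 is descriptive, and whole-trajectory nonuse is defensible there.

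**Conclusion.** The concern holds for objective 3. Followed as written, the plan gives a care home hazard ratio below 1 when the program has no effect. The direction follows from the stated definitions and does not depend on the assumed rates. The size does: across mean waits of 1 to 24 months, with the assumed admission, death and attendance shares, the null hazard ratio runs from about 0.97 to 0.62. With the expected sample, even the mild end of that range could look precise and significant. Because the article itself fixes the control definition, the stated origin and the model term, an analysis plan that follows them would reproduce the bias. It should be corrected before the effect analyses are run.

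**What to change.** Confine the change to objective 3 and leave the nonuse definition as it is for objective 2.

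1. **One time zero per matched pair**, at the attendee's first attendance. Match to a person who on that date is alive, in the community and not yet attending, at a similar time since first RAI-HC, with covariates from the last RAI-HC before that date. Run the outcome clock from that date for both.
2. **Controls defined as not having attended by time zero.** Keep later starters in the comparison group for the main analysis. In a sensitivity analysis, censor them when they start and apply inverse-probability weights.
3. **Alternative to 1 and 2:** a model with attendance as a time-dependent exposure.
4. **Use classes in the effect models:** form them only from attendance before a landmark and start follow-up at that landmark, or enter cumulative use as a time-varying term. Realigning the pairs alone does not cure classes built on later attendance.

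The registries already hold the start, stop and attendance dates, so no new data or participants are needed. The cost is revised wording, reprogramming of the matching and models in each province, and a slightly diluted contrast because some controls later attend.

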#### Study Outcomes

The data sources noted above enable us to examine a range of important study outcomes. Data on the time between a person’s first RAI-HC assessment and admission to a care home will come from provincial continuing care registries. Symptoms of depression will be assessed using the validated RAI-HC Depression Rating Scale [72], with scores ranging from 0 to 14 and a cut point of 3 or higher representing clinically meaningful depressive symptoms [72,73]. We will capture physical and cognitive decline, using validated RAI-HC scales [64]: the Activities of Daily Living Hierarchy (ADLh) Scale [74] and the Cognitive Performance Scale (CPS) [75]. Both scales range from 0 (no impairment) to 6 (maximum impairment), and our outcomes will be dichotomous, indicating any increase (vs no change or a decrease) between the previous and follow-up measurement in each of these scales. Using care practitioner claims data, we will generate rates of different types of primary and specialist care use (eg, family physician, specialists, nursing practitioner, and allied health providers). We will use the DAD and NACRS databases to generate rates of emergency department registrations, hospital admissions, and days in hospital (including alternative level of care) [43]. Rates will be stratified by day program use or nonuse pattern.

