Despite these variations, day programs have unique characteristics that set them apart from other continuing care options. Day programs employ care staff and admit people with a certain level of support needs [30,33]. This distinguishes them from senior or community centers [34] and creative arts programs [35], which are open to independent older adults, do not employ care staff, and are organized more informally. Unlike home care [36] or in-home respite [37], day programs serve groups of older adults in a setting external to the attendee’s home [30,33], supporting social interactions and caregiver respite [32]. Unlike geriatric day hospitals, which provide medical, therapeutic, and rehabilitative care for a few weeks [38], day programs prioritize social and recreational activities, and they do so for long term (often for months or years) [30,33]. Day program services and supports usually include transportation; meals; recreational activities (eg, playing games, musical activities, crafting, and painting); socializing with other clients and day program staff; physical, cognitive, and spiritual activities; social work counseling; and case management support. Personal, nursing, and medical care are often not provided, or only to a limited extent, depending on the program and health system.

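### Objective 3 assigns all follow-up to a use class fixed over the whole trajectory, so time after attendance stops stays with attendees and class differences cannot be read as dose-response

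*Protocol article*

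**What the plan says.** All references are to the protocol article.

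- **Exposure.** The use class comes from four variables that summarise the person's attendance. They include "total number of days a person attended a day program" and a flag "indicating whether a person consistently attended a day program or whether there were longer periods (several weeks) of nonattendance". The reference state is equally permanent: "Nonuse will be defined as no day program exposure at any time during a person’s continuing care trajectory". A person who has stopped attending never returns to nonuse.
- **Available dates.** The same section describes the continuing care registries as "documenting the dates a person starts or stops attending a day program, days of attendance, and the duration of each visit". These data are used to build the class.
- **Outcomes and models.** For service use, Study Outcomes states: "Rates will be stratified by day program use or nonuse pattern". For care home admission, Objective 3 states: "Each model will include day program use or nonuse class as independent variable and will be adjusted for time-varying variables". What varies with time there is the adjustment set, not the exposure. The GEE models for the other outcomes use the same class term.
- **Follow-up.** Setting and Sample: "We will follow everyone until they move into a care home, are lost to follow-up", or until December 31, 2024. Stopping attendance is not among the end points.
- **Length of attendance.** The Introduction says of day programs that "they do so for long term (often for months or years". No distribution of attendance duration is given.

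**The concern.** A person who attends briefly and then stops can contribute years of emergency visits, admissions and decline to the attendee side. The class tells the model how much a person attended in total. It does not tell the model whether a given event fell during attendance or after it. For a given length of follow-up, the off-program share is largest in the classes with the fewest attended days.

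Two things are at stake. First, the estimate mixes program effect with follow-up length, so 2012 and 2021 entrants would give different answers for the same program. Second, the third objective lists use class as a possible effect modifier. If every class benefits equally while attending, unequal off-program shares can still produce a finding that more use works and less use does not. Health systems could act on that finding.

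**Working it through.** **Follow-up range.** Initial assessments run from January 1, 2012 to December 31, 2021, and data end on December 31, 2024. The earliest entrant has 13.0 years of potential follow-up and the latest 3.0. This agrees with the minimum of 3 years stated in Setting and Sample. Thirteen years is a maximum, not a typical value.

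**Assumed inputs.** The documents give no attendance durations, stopping rates or event rates. Everything below is illustrative, except that the hazard ratio of 0.6 is the plan's own planning value.

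**Rates.** With a constant background rate, an on-program rate ratio RR_on, and no effect after stopping:

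average RR = 1 − (1 − RR_on) × (months on program / months followed)

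Take RR_on = 0.70 in every class and 48 months of follow-up:

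- 6 months on program: 1 − 0.30 × 6/48 = 0.96
- 36 months on program: 1 − 0.30 × 36/48 = 0.78

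The benefit while attending is identical, but the reported ratios differ.

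**Care home admission.** Assume an admission hazard of 0.08 per year in nonattendees and a death hazard of 0.12 per year in both groups. The attendee admission hazard is 0.6 × 0.08 = 0.048 while on program and 0.08 afterwards. The large-sample Cox estimate is exp(b), where b solves ∫[S1·h1 − p·(S1·h1 + S0·h0)]dt = 0 with p = S1·e^b / (S1·e^b + S0). Here h is the admission hazard and S the probability of still being at risk (1 = attendee, 0 = nonattendee).

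| Time on program | 3 years of follow-up | 13 years of follow-up |
|---|---|---|
| 1 year | 0.84 | 0.92 |
| 2 years | 0.71 | 0.86 |

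**Direction.** A separate simulation of 400,000 persons used other assumed inputs: admission hazard 0.15 per year, death or loss 0.08 per year, mean wait to first attendance 1 year, mean attendance 1.5 years, and administrative censoring at 3 to 13 years. Rate ratios are against never-attenders; class results run from low to high use.

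1. True ratio 0.6 while attending and 1 afterwards, classes by intended duration, post-start time only: 0.97, 0.92, 0.87, 0.74. Carry-over produces attenuation and a gradient.
2. Same set-up with no true effect: 0.99, 1.01, 1.01, 0.98. Carry-over alone produces no gradient.
3. No true effect, classes by days actually accumulated, counted from first attendance: overall 1.00, classes 1.36, 1.22, 1.00, 0.64. People who stay out of a care home longer accrue more days, and this alone creates a gradient.
4. As in 3, but counted from the first assessment, as planned for care home admission: overall 0.74, classes 0.95, 0.88, 0.75, 0.51. Pre-attendance time, which is event-free by construction, adds an apparent benefit.
5. True ratio 0.6 while attending, with the hazard doubled after stopping (people stop because they decline): overall 1.43 counted from first attendance and 1.04 counted from the first assessment. The estimate reaches or crosses 1 despite a real on-program benefit.
6. With follow-up split into current and past attendance, the set-up with a true ratio of 0.6 returns 0.61 for current attendance, and the null set-up returns 0.99.

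**The case against.** The best defence is that this is a choice of question. Keeping people in their group after they stop is a legitimate ever-attended contrast. It suits an objective phrased as later care home entry, and it avoids the bias that arises when people stop because they decline. On that question, longer attenders really do receive more benefit over follow-up, so a gradient is not false in itself. This stands in part: the contrast is acceptable if declared, but the article does not declare it, and its value still shifts with entry year.

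It can also be said that stop dates are not ignored, because total days and the interruption flag enter the class. That is correct. However, they enter as one label per person, which cannot place an event before or after stopping. No sentence says outright that post-stop time counts as exposed; this follows from the class definition, the model term and the follow-up rule together. These are stated choices, not details left to an analysis plan.

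The size is wholly assumed. Attendance that ends at care home entry or death leaves no post-stop time, and many people will be followed for far less than 13 years. This stands, and it limits the figures to illustrations.

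A reader might infer that effects must shrink toward none, or that carry-over manufactures a dose-response where no effect exists. The documents support neither. Attenuation needs the effect to end at stopping and stopping to be unrelated to prognosis, and the article says nothing on either. Results 2 and 3 show that a gradient under no effect comes from classing people by days accrued during follow-up, not from carry-over.

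**Conclusion.** The point holds in this form. The exposure is fixed from the whole trajectory, time after stopping stays with the attendee class, and the objective 3 estimates depend on how long people are followed after they stop. Under the two conditions just named, a hazard ratio of 0.6 lasting one year would appear as about 0.84 over 3 years and 0.92 over 13, and equal on-program benefit would look graded across classes. If decline drives stopping, the bias can reach or cross 1. Pre-attendance time, which is a separate matter, pushes the other way. The net direction therefore cannot be predicted, and differences between whole-trajectory classes cannot be read as dose-response. This should be corrected before analysis; it does not invalidate the study.

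**What to change.** 1. Name the whole-follow-up class contrast as an ever-attended effect and state that it includes time after stopping.
2. Report the attendee versus nonattendee contrast over a common fixed horizon from the same start for both members of a pair: for example 12 months, and 36 months where potential follow-up from that start allows. Three years is assured only from the first RAI-HC assessment, not from a later eligibility assessment used as the index date. For care home admission, give cumulative admission and mean time at home within the horizon. A fixed horizon does not remove off-program time (0.84, not 0.6, in the one-year example over 3 years). It makes the estimate interpretable and comparable across entry years.
3. As a supporting analysis, use the registry start and stop dates to split follow-up into current and past attendance, with the matched nonattendee split at the same elapsed time. State that stopping because of decline can bias this split.
4. Do not interpret differences between whole-trajectory classes as dose-response. Base any class contrast only on attendance before the outcome time at risk begins.

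The cost is wording and some programming in each province; the dates are already held. The downside is that late follow-up leaves the fixed-horizon contrast, though it is kept in the ever-attended one.
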